**Methods/Design:**

One hundred and seventy six eligible participants suffering from current MDE are being randomised into a dietary intervention group or a social support group. Depression status is assessed using the Montgomery–Åsberg Depression Rating Scale (MADRS) and Structured Clinical Interview for Diagnostic and Statistical Manual of Mental Disorders (Non Patient Edition) (SCID-I/NP). The intervention consists of 7 individual nutrition consulting sessions (of approximately 60 minutes), delivered by an Accredited Practising Dietitian (APD). Sessions commence within one week of baseline assessment. The intervention focuses on advocating a healthy diet based on the Australian Dietary Guidelines and the Dietary Guidelines for Adults in Greece. The control condition comprises a befriending protocol using the same visit schedule and length as the diet intervention. The study is being conducted at two locations in Victoria, Australia (a metropolitan and regional centre). Data collection occurs at baseline (pre-intervention), 3-months (post-intervention) and 6– months. The primary endpoint is MADRS scores at 3 months. A cost consequences analysis will determine the economic value of the intervention.

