### Study aims

We aim to investigate the efficacy of dietary improvement in the treatment of MDE. The primary outcome includes changes in MDE using the Montgomery-Åsberg Depression Rating Scale (MADRS). Secondary outcomes include; depressive and anxiety symptoms, functioning, quality of life, and changes in targeted dietary behaviours, cardiovascular and metabolic risk. A secondary aim is to evaluate the cost efficacy of the intervention from a societal perspective at 3 months.

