### Data collection and outcome measures

Table 
1 displays the outcome measures and corresponding timepoints. Demographic data (including age, sex, post code, contact details, nominated General Practitioner (GP)), psychiatric, and self-report measures are obtained from each participant at baseline and post intervention (3-months) to determine depressive and anxiety symptoms, functioning and quality of life (using the Assessment of Quality of Life 8 dimension [AQoL8D]
[25]) which will also allow the calculation of quality-adjusted life-years (QALYs). Clinical data such as blood pressure and anthropometric measures including height, weight and waist circumference are also taken. Habitual dietary patterns are collected as stated above. The IPAQ
[24] and self-report smoking questionnaire are completed. At 6-months, participants are contacted via telephone during which time RAs re-administer the MADRS, Hospital Anxiety and Depression Scale (HADS)
[26] and DST. At this time, participants initially assigned to the control condition are offered the resources developed and used by the APD for the diet intervention.

**Table 1 T1:** Schedule of measurements

**Variable**	**Instrument**	**Time point**

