### Data analyses

Data analysis will be conducted by a researcher blinded to the treatment conditions. A one-tailed analysis will be used to detect differences in MADRS scores between the intervention and control groups. Analyses will explore dose–response effects associated with intervention diet adherence. The primary efficacy analysis will assess average treatment group differences for the primary outcome measure (MADRS) over the entire study period and use a likelihood based mixed-effects model, repeated measures (MMRM) approach at each time point. Analysis of covariance (ANCOVA) will be used to compare differences between treatment means in changes from baseline to follow up. Intention to treat analysis will be employed. To assess confounding, covariates will include age, gender, Body Mass Index (BMI) physical activity levels, smoking and alcohol consumption. Non-parametric statistics will be used when assumptions for parametric methods are violated. Effect sizes will be calculated using Cohen’s guidelines. All tests of treatment effects will be conducted using an alpha level of 0.05 and reporting 95% confidence intervals. Multiple imputation will be employed for the management of missing data.

The economic evaluation will compare the dietary intervention to its comparator (the befriending group) in terms of both the costs and consequences as assessed by an incremental cost-effectiveness ratio (ICER). The primary study design is that of a cost consequence analysis (CCA)
[33].

Standard Australian unit costs (i.e. Medicare Benefits Schedule) will be applied to the resource use units collected. Costs will be presented in total and disaggregate forms such as those falling upon the health sector, patients, government and other sectors. The technique of ‘bootstrapping’ will be used to obtain confidence intervals for cost effectiveness ratios, since parametric techniques are inappropriate for use on skewed variables and ratios. The sensitivity of the results will also be tested against the variation in the utility weights and unit cost prices.

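### The primary economic design is a cost-consequence analysis, yet value is assessed by an ICER with no named denominator and a bootstrap interval on the ratio, which cannot be interpreted unless the effect difference is clearly non-zero

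*Protocol article*

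**What the plan says.** The economic aim, under Study aims, is to "evaluate the cost efficacy of the intervention from a societal perspective at 3 months".

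Data analyses describes the evaluation in two consecutive sentences. The first compares the diet and befriending groups "in terms of both the costs and consequences as assessed by an incremental cost-effectiveness ratio (ICER". The second states: "The primary study design is that of a cost consequence analysis (CCA". The abstract mentions only the latter: "A cost consequences analysis will determine the economic value of the intervention".

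For uncertainty, Data analyses says that bootstrapping will "be used to obtain confidence intervals for cost effectiveness ratios, since parametric techniques are inappropriate for use on skewed variables and ratios". It adds that results will be tested for sensitivity to utility weights and unit costs.

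No effect measure is named as the denominator of the ICER. Data collection and outcome measures says of the AQoL-8D only that it is an instrument "which will also allow the calculation of quality-adjusted life-years (QALYs". Table 1 schedules it at baseline and 3 months. Cost-utility analysis appears in the abbreviation list but is not used in the text.

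**The concern.** There are two linked problems.

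**Design.** A cost-consequence analysis sets costs and several outcomes side by side and leaves the weighing to the reader. An ICER needs one chosen effect measure. The article makes the ratio the means of assessment without saying that it is supplementary or which outcome it uses.

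**Uncertainty.** The reason given for the bootstrap is half right. Resampling avoids normal-theory assumptions about skewed costs, but the difficulty with an ICER is not skewness. The ratio is discontinuous where the effect difference is zero, and its sign does not identify the quadrant. A positive ratio can mean dearer and better or cheaper and worse; a negative one can mean dominant or dominated. Once replicates spread over several quadrants, ordering them by the ratio does not order them by value, and an interval read from the ratios has no clear meaning.

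At stake is the headline uncertainty statement for the cost-efficacy aim. It would be hardest to read when the effect is modest, which is when a decision-maker most needs it.

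**Working it through.** The article gives no ICER, QALY difference, utility SD, cost SD or threshold, so it has no figure to reproduce. What follows is an illustration.

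**From the article:** 70 evaluable per group (Sample size); AQoL-8D at baseline and 3 months (Table 1); 3-month economic horizon (Study aims).

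**Assumed:** QALYs as the denominator; linear area under the curve over 0.25 year; utility SD 0.15, 0.20 or 0.25; correlation of 0.5 between baseline and 3-month utility, with baseline adjustment; 3-month utility gains of 0 to 0.10.

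**Step 1, one ratio with two meanings.** +300 / +0.00625 = 48,000 and −300 / −0.00625 = 48,000. The first is dearer and better, the second cheaper and worse.

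**Step 2, standard error.**
- QALY difference = 0.5 × 0.25 × gain = 0.125 × gain.
- SE(utility) = SD × √(1 − 0.5²) × √(2/70) = 0.0220, 0.0293, 0.0366 for the three SDs.
- SE(QALY) = 0.125 × SE(utility) = 0.0027, 0.0037, 0.0046.

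The factor 0.125 is in both the difference and its SE, so it cancels. What matters is z = gain / SE(utility), not how small the QALY difference is in absolute terms.

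**Step 3, share of replicates with a non-positive denominator.** If the observed estimate equals the gain, the share is approximately Φ(−z).

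| Utility gain | SD 0.15 | SD 0.20 | SD 0.25 |
|---|---|---|---|
| 0 | 50% | 50% | 50% |
| 0.03 | 8.6% (z = 1.37) | 15.3% (1.02) | 20.6% (0.82) |
| 0.05 | 1.1% (2.28) | 4.4% (1.71) | 8.6% (1.37) |
| 0.10 | <0.1% (4.55) | <0.1% (3.42) | 0.3% (2.73) |

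A share above 2.5% is equivalent to a 95% interval for the effect that includes zero. To stay clear of it, the observed gain must exceed 1.96 × SE(utility), which is 0.043, 0.057 and 0.072 for the three SDs.

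**Step 4, sensitivity.** Without baseline adjustment, SE(utility) = SD × √(2/70) = 0.0254, 0.0338, 0.0423. The share is then 2 to 12% at a gain of 0.05 and still under 1% at 0.10. With 75 per arm in place of 70 (unadjusted, SD 0.20, gain 0.05) it moves only from 7.0% to 6.3%.

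**Step 5, what the interval looks like.** A bootstrap was simulated without baseline adjustment: 70 per arm, utility SD 0.20, lognormal costs with mean 1,500 and coefficient of variation 1.5, cost difference +300, percentile limits. The costs and the percentile method are further assumptions.
- Gain 0.05, true ICER 300 / 0.00625 = 48,000: the median interval was roughly −0.5 to +0.6 million per QALY. The effect interval spans zero in about Φ(1.96 − 1.48) = 68% of trials.
- Gain 0.10, true ICER 300 / 0.0125 = 24,000: the median interval was about −44,000 to +129,000. The effect interval spans zero in about Φ(1.96 − 2.96) = 16% of trials.

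At a gain of 0.05 the percentile interval still covered the true ratio in about 98% of simulated trials. The fault is therefore in what the interval means, not in its coverage.

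**The case against.** - **The denominator is inferred.** The article speaks of ratios in the plural and never says cost per QALY. Ratios per MADRS point would also fit. This stands: the utility-weight sensitivity analysis points to QALYs but does not settle it, and the percentages apply only to QALYs. The argument itself holds for any effect measure that is close to zero relative to its standard error.
- **A short horizon does not cause the problem.** A reader might infer that 3-month QALYs are so small that the ratio must fail. Step 2 shows otherwise, because the time factor cancels.
- **The failure is conditional.** At a gain near 0.10 the denominator rarely changes sign. This stands. In that case the negative lower limit also owes much to the cost side, where the assumed difference of 300 has an SE of 2,250 × √(2/70) ≈ 380.
- **A cost-consequence analysis may be accompanied by ICERs.** True, so the two sentences are unreconciled rather than incompatible.
- **Details may sit elsewhere.** The article does not specify percentile limits, and net benefit or a plane may be in a plan not shown. Their absence is no fault. That does not excuse the method the article does fix, an interval on the ratio, or the reason it gives for it.

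**Conclusion.** The point holds in a limited form. The article leaves the relation between its cost-consequence analysis and its ICER unresolved, names no denominator, and commits to a bootstrap interval on a ratio. That interval cannot be interpreted if the effect difference is not clearly separated from zero. Under the assumed inputs this is a real prospect at utility gains of 0.03 to 0.05 and largely disappears near 0.10. The document supplies no utility SD, correlation or expected gain, so the percentages show the mechanism and do not forecast the result.

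A reader might go further and conclude that the trial could not meet its cost-efficacy aim. The documents do not support that. The abstract rests economic value on the cost-consequence analysis, and Data analyses promises costs in total and disaggregated by who bears them. Those results survive an unreadable ratio interval. The aim is secondary, and the MADRS analysis and data collection are untouched. The change is worth making before analysis but is not critical.

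**What to change.** Reword the economic paragraph in Data analyses, and carry the wording into the analysis plan:

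1. Keep the cost-consequence analysis as primary and stop describing it as assessed by an ICER.
2. Label any ICER as supplementary, state its denominator, and report it as a point estimate only.
3. Bootstrap incremental cost and incremental effect jointly, by participant within arm, adjusting for baseline utility where QALYs are the effect.
4. In place of an interval on the ratio, report incremental net benefit with its 95% confidence interval over a stated range of thresholds, with the cost-effectiveness plane and acceptability curve.

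Net benefit is linear in cost and effect, so it remains well defined when the effect difference crosses zero. The same replicates serve every output and no new data are needed. The cost is a little more analysis work and the need to state threshold values in advance.

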## Discussion

It is well-accepted that significant numbers of people with depression fail to respond to pharmacological and/or psychological treatments. It has been suggested that lifestyle components, including diet quality, play a role in the genesis of depression and that lifestyle is an important, yet neglected, intervention target for the treatment of MDE. However, there have been no comprehensive studies to date that have specifically sought to answer the question “if I improve my diet will I feel less depressed?” What is an increasingly common question, both in clinical practice and the general community, remains unanswered to date and this is an important gap in our knowledge base. Our study will provide essential evidence regarding the efficacy and cost-efficacy of dietary improvement in the treatment of depressive illness, thus allowing for the development of treatment strategies incorporating dietary improvements. Addressing lifestyle factors may additionally contribute to secondary prevention, as well as overlapping heavily with validated strategies for the management of other highly prevalent medical conditions such as CVD, obesity and type 2 diabetes. These are conditions associated with depressive illness, and may share common underlying pathways. A dietary intervention for depression as an adjunct to standard care, has the potential to be cost-effective, highly acceptable and widely applicable. This approach may lead to improved outcomes for individuals with MDE and reduce the public health burden of psychiatric illness.

## Abbreviations

CVD: Cardiovascular disease; MDE: Major Depressive Episodes; MADRS: Montgomery–Åsberg Depression Rating Scale; DSM-IV-TR: Diagnostic and Statistical Manual of Mental Disorders 4; SCID-I/NP: Structured Clinical Interview for Diagnostic and Statistical Manual of Mental Disorders (Non Patient Edition); DST: Dietary Screening Tool; SAPAS: Standardised Assessment of Personality – Abbreviated Scale; FFQ: Food frequency questionnaire; CCVFFQ: Cancer council victoria food frequency questionnaire; APD: Accredited Practising Dietitian; CTC: Clinical Trial Co-ordinator; RA: Research Assistant; IPAQ: International Physical Activity Questionnaire; GP: General practitioner; AQoL8D: Assessment of quality of life – 8 dimension; QALYs: Quality-adjusted life-years; CRFs: Case report forms; MMRM: Mixed-effects model, repeated measures; ANCOVA: Analysis of covariance; BMI: Body Mass Index; ICER: Incremental cost-effectiveness ratio; CCA: Cost consequence analysis; CUA: Cost-utility analysis
